#### Methodological outcomes

To assess contrasts in physical activity levels between the intervention and control group, we will compare changes in physical activity levels within the control group to changes in the intervention group using analysis of covariance (ANCOVA) or mixed linear regression models adjusted for baseline for the analyses of repeated outcomes [38].

Participation rate, intervention compliance, retention and drop-out will be compared to findings in previous conventional exercise-oncology RCTs. For instance, a systematic review reported median (IQR) rates of uptake, adherence and completion of exercise programmes in patients with cancer of 63% (33–80%), 84% (72–93%) and 87% (80–96%), respectively [39]. More recent and relevant publications, if available, will also be taken into account. Comparisons will be done by using the chi-squared test or independent samples *t* test.

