### Patients

We will make use of the UMBRELLA cohort, which aims to generate short-term and long-term data on clinical and patient-reported outcomes during and after breast cancer treatment and to provide infrastructure for multiple randomized evaluations of the intervention in patients with breast cancer [25]. Recruitment started in September 2013 at the University Medical Centre (UMC) Utrecht and all patients with breast cancer who are referred to the department of radiation oncology of the UMC Utrecht for radiation treatment are asked to participate in the UMBRELLA (see Figs. 1 and 2) [25]. They give consent for the use of routinely collected clinical data and prospective collection of patient-reported outcome measures through regular questionnaires. In addition, they can opt to give consent to be randomized for future intervention studies within the cohort. Patients will be informed that they will be offered an experimental intervention if they are randomly selected for the intervention group. They are also informed that they will not be contacted when randomly selected for the control group and that their data can be used in a trial context [20]. Between the start of recruitment and July 2016, 88% of the eligible patients who were invited for participation in UMBRELLA gave consent to participate and 87% of those who agreed to participate also consented to be randomized for future intervention studies within the cohort [25].

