### Endpoints

#### Methodological endpoints

##### Acceptance of the intervention

Acceptance of the intervention is defined as the percentage of patients who are randomized to the exercise intervention and accept participation.

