### Statistical analyses

#### Sample size calculation

The sample size calculation is based on the intention-to-treat analyses of the primary effectiveness outcome QoL (EORTC-QLQ-30) [30]. Here, we determine a clinically relevant difference as a difference of 10 points [30]. A difference of 10 points is realistic because in a previous exercise trial in patients with cancer, QoL in the intervention group improved by 15.1 points (SD 17.7) and in the control group by 6.1 points (SD 17.1) using the EORTC-QLQ-30 after the 12-week intervention [34, 35]. Therefore, using the control group data from the previous trial and the 10-point difference, we assume a 6-point increase in QoL in the control group and a 16-point increase in the intervention group, among patients who accept the intervention in this cmRCT. We expect an attendance rate of 70% in the intervention group and assume that the improvement in non-attenders randomized to the intervention group (30%) is equal to the improvement in the control group (i.e. 6 points). Furthermore, we assume that non-attendance does not impact the standard deviation. As a result, we estimate a mean improvement of 13 points in the intervention group ((70*16 + 30*6)/100 = 13) instead of 16 points and a mean improvement of 6 points in the control group. Using these numbers, standard deviations of 17.7 and 17.1, power of 80% and alpha of 0.05, we calculated that 98 patients are needed in each group.

As we will use linear regression analyses adjusted for baseline, the correlation between baseline and follow up needs to be taken into account in the sample size calculation. Therefore, the calculated number of subjects should be multiplied by (1-*ρ*
^2^), plus one extra subject per group [36], where *ρ* represents the correlation between baseline and follow-up outcomes. In our previous trials [34, 35], we identified correlation of 0.4 between baseline and follow-up QoL. This leads to a final sample size of 83 patients per group (98*0.84 + 1). As recommended by Candlish [37], we will update the sample-size calculation before the end of the trial when the actual acceptance rate of the intervention deviates from the estimated rate and adapt the sample size accordingly.

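### Participation and retention are to be tested against published conventional trials without a common denominator, by chi-squared or t tests that ignore between-trial variation

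*Protocol article*

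**What the plan says.** Feasibility is the first aim (Aim of this study), and participation rate is among its first listed components. Under Acceptance of the intervention, the endpoint is "the percentage of patients who are randomized to the exercise intervention and accept participation". Under Trial retention, drop-out in the intervention group is counted from signature of the UMBRELLA Fit consent form, so patients who refuse after randomization are not in that rate.

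The Patients section describes the consent steps that come first: "88% of the eligible patients who were invited for participation in UMBRELLA gave consent to participate and 87% of those who agreed" also agreed to be randomized in future studies.

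Under Methodological outcomes: "Participation rate, intervention compliance, retention and drop-out will be compared to findings in previous conventional exercise-oncology RCTs". The example given is a systematic review with median (IQR) uptake of 63% (33–80%), adherence of 84% (72–93%) and completion of 87% (80–96%). More recent publications may be added. The paragraph ends: "Comparisons will be done by using the chi-squared test or independent samples" t test. No common denominator is fixed and no allowance for variation between trials is stated.

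**The concern.** In this design, unwillingness to take part in research or to be randomized is filtered out at cohort entry, before the acceptance denominator begins. The article itself says that invited patients decide only about the exercise programme, and that in a conventional trial some patients refuse because of the 50% chance of control. Setting one rate beside the other without aligning denominators can make the new design look better, or worse, for reasons unrelated to patients' willingness to exercise.

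Retention raises the same issue. In a conventional trial, consent precedes randomization, so drop-out after consent and drop-out after randomization cover much the same people. Here they differ by everyone who declines the offer.

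The tests add a second problem. They treat published results as one homogeneous sample, although the cited uptake rates differ greatly between trials. At stake is what is reported on participation and retention, both part of the first aim.

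**Working it through.** **Inputs.** Consent to cohort 88% and to randomization 87% (Patients). Expected acceptance 70% (Sample size calculation, where it is called attendance, although the planned update there is tied to the acceptance rate). Uptake 63%, IQR 33–80%, and completion 87% (Methodological outcomes). Final size 83 per group.

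**1. The plan's own sample size.** It rests on "standard deviations of 17.7 and 17.1, power of 80% and alpha of 0.05, we calculated that 98 patients are needed in each group", with "we estimate a mean improvement of 13 points in the intervention group" and "a mean improvement of 6 points in the control group", a difference of 7.
- Pooled SD = √((17.7² + 17.1²)/2) = 17.40.
- n = 2 × (17.40 × (1.960 + 0.842)/7)² = 97.02, rounded up to 98.
- The article also states "we identified correlation of 0.4 between baseline and follow-up QoL", so 98 × (1 − 0.4²) + 1 = 83.3, giving 83.

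Both figures reproduce with a two-sided alpha. The sample size is not in question; 83 is used below.

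**2. Participation on different denominators, at 70% acceptance.**

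| Denominator | Calculation | Rate | Against 63% |
|---|---|---|---|
| Randomized to intervention | as defined | 70.0% | +7.0 points |
| Cohort participants | 0.87 × 0.70 | 60.9% | −2.1 points |
| Invited to the cohort | 0.88 × 0.87 × 0.70 | 53.6% | −9.4 points |

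The sign changes for any acceptance between 63% and 0.63/0.7656 = 82.3%, or between 63% and 0.63/0.87 = 72.4% with the randomization-consent step alone. The planned 70% lies in both ranges.

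**3. The opposite direction.** The final eligibility check comes after randomization and only for patients willing to take part (Recruitment and allocation). The Discussion accepts that some randomized patients may not meet the criteria. Removing them from the denominator raises the rate. The ineligible share is not given, so as an assumption:
- 10% ineligible: 0.536/0.90 = 59.5%.
- 15% ineligible: 0.536/0.85 = 63.0%, and the deficit is gone.

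**4. Retention.** If 87% of accepters complete (the review's median, used for illustration), that is 0.87 × 0.70 = 61% of all patients randomized to the intervention.

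**5. Inputs for the tests.** A chi-squared test needs counts and a t test needs means and SDs. A median with IQR gives neither.

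**6. Dependence on the comparator.** Take 58/83 accepting (69.9%; 95% CI 58.8–79.5%).
- Against a fixed 63%, the exact binomial p is 0.21.
- With an assumed comparator size from 83 to 3163, chi-squared p runs from 0.32 to 0.20.
- At an assumed size of 3163, the same 58/83 gives p < 0.0001 against the lower quartile (33%) and p = 0.024 against the upper quartile (80%), in opposite directions.

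**7. Between-trial spread.** The sampling SE is √(0.7 × 0.3/83) = 5.0 points. Suppose this trial were simply one more draw from the population of conventional trials. In simulation, a nominal 5% test against a fixed 63% then rejects about 37%, 62% or 77% of the time for assumed between-trial SDs of 10, 20 or 35 points. The upper value is a normal approximation from the IQR, 47/1.349 = 35.

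**The case against.** The strongest reply is that the benchmark's denominator is unknown. The article describes the 63% as uptake of exercise programmes; if it means programme uptake among those offered, the acceptance rate is already close to the matching quantity. The 88% and 87% are rates for the whole cohort at radiotherapy referral. They reflect refusal of data collection and of any future randomization, not of an exercise trial in inactive patients 12 or 18 months later. All of this stands. A reader might infer that 53.6% is the properly matched figure, or that the comparison necessarily favours the cohort design. The documents support neither.

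A reader might also set the 35-point spread against the 5-point SE and infer that uncertainty is understated sevenfold. That does not follow. The 35 assumes normality for a bounded, skewed rate and includes within-trial sampling error. It is also the SD of single trials; for a comparison with the average of k trials the relevant term is nearer 35/√k, and k is not given.

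Finally, the review is only an example, single trials with counts would permit a chi-squared calculation, and the sentence on tests may also be meant for the generalizability comparison with individual patient data. This softens the point but does not remove it. The sentence closes the paragraph on participation, compliance, retention and drop-out, and a test against one chosen trial still ignores how much trials differ. Nor is this merely detail left to an analysis plan: the article itself fixes the endpoint definitions, the comparator and the tests.

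**Conclusion.** The point holds in a limited form. The acceptance and retention rates, as defined, may not share a denominator with conventional trials, and the stated tests are unsuited to the comparison. At the expected 70%, the apparent 7-point advantage could become a deficit of about 2 to 9 points. That requires the 63% to count patients approached for a trial and the cohort-wide consent rates to hold for patients who later become eligible. Ineligibility found after randomization would shrink or remove the deficit. The direction is therefore open, which is the reason to state denominators.

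Whatever the direction, a p-value that ignores an uptake IQR of 33–80% would overstate the certainty of any difference; by how much cannot be fixed from the documents.

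A reader might infer that the whole feasibility conclusion can reverse. The article sets no threshold or decision rule for participation, and the randomized physical activity contrast and the generalizability comparison are untouched. Only the participation and retention part is affected. This is a cheap improvement, not a flaw in the trial's effectiveness analysis.

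**What to change.** Amend Methodological outcomes in three respects.

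- Report participation and retention with 95% confidence intervals on named denominators: all invited to the cohort, all consenting to randomization, all randomized to the intervention, those eligible after the final check where known, and accepters. The figures counted from cohort invitation are products of rates from different sets of patients, so their intervals should carry the uncertainty of each step.
- For each comparator study, state its denominator and use the matching rate from this trial. Where a comparator's denominator cannot be established, say so and show the range.
- Replace the chi-squared and t tests for these comparisons with a descriptive one: this trial's rate and interval against the between-trial range, or against a random-effects prediction interval where counts are available.

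The cost is a few lines of wording. The cohort consent rates are already reported and the remaining counts arise in the running of the trial; where post-randomization eligibility was not recorded, that row stays incomplete. Sample size and outcome data are unchanged. The downside is a possibly less favourable headline participation figure.

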#### Effectiveness outcomes

To assess differences in changes from baseline to 6 months in patient-related outcomes (QoL, fatigue, anxiety and depression and sedentary behaviour) between intervention and control, we will use intention-to-treat linear regression analyses adjusted for baseline. Mixed linear regression models adjusted for baseline will be used for the analyses of repeated outcomes (i.e. 6–24 months follow up).

The continuous within-group measurements in the intervention group, i.e. cardiorespiratory fitness, anthropometrics and patient-reported outcomes, will be analysed by the paired *t* test (if normally distributed) or Wilcoxon signed-rank test (if skewed).

From all UMBRELLA participants meeting the inclusion criteria for UMBRELLA Fit, we randomly selected patients for the intervention or control group with a 1:1 ratio. Besides comparison between patients in the intervention group and patients in the control group, we will investigate whether intervention effects change if we compare patients in the intervention group with all patients within UMBRELLA who are eligible for the UMBRELLA Fit study. Also, the timing of the regular measurements relative to the start and end of the intervention may vary between patients in the intervention group. Therefore, we will also assess QoL immediately at the start and end of the intervention. We will compare these outcome measures with the outcome measures from the regular UMBRELLA measurements completed before the start of the intervention and 6 months later (different and longer measurement intervals).

Patients may refuse the intervention after randomization and thus receive standard care. As a result, the estimated effect of the intervention may be diluted. We will conduct instrumental variable (IV) analyses [40, 41], taking non-compliance into account and assuming that the improvement in non-attenders randomized to the intervention group is equal to the improvement in the control group and that it does not impact the standard deviation. The IV method evaluates the effect of an intervention among “compliers”, who are individuals who would have received the intervention if it had been offered to them.

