### Recruitment and allocation

UMBRELLA participants meeting the inclusion criteria will be randomly allocated to the intervention or control group with a 1:1 ratio, by an independent data manager using a computer-generated randomization list. Randomization will be stratified for time since enrollment (12 or 18 months). Patients randomized to the intervention group will receive an offer by mail to participate in an exercise programme, a patient information sheet and an informed consent form. After 1–2 weeks these patients are contacted by telephone to further explain the study. If patients decide to participate, a last check of eligibility will be performed. Contra-indications to the exercise programme will be screened using the Physical Activity Readiness Questionnaire (PAR-Q) [27]. If eligible, they will be invited to visit the UMC Utrecht to sign the informed consent form for the UMBRELLA Fit study and undertake a baseline assessment. If patients refuse to participate because of bad timing of the invitation, they will be asked if they are willing to start later. Patients randomized to the control group will not be informed about the study. Recruitment started in October 2015.

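### Randomisation is stratified by time since enrolment (12 or 18 months), but the stated outcome models name only baseline as an adjustment; adding the stratum is a small, free improvement

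*Protocol article*

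**What the plan says.** Under Recruitment and allocation, eligible cohort members are "randomly allocated to the intervention or control group with a 1:1 ratio", and "Randomization will be stratified for time since enrollment (12 or 18 months". This is the only stratification factor given.

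Under Effectiveness outcomes, the 6-month comparison of QoL, fatigue, anxiety and depression, and sedentary behaviour is specified as follows: "we will use intention-to-treat linear regression analyses adjusted for baseline". For longer follow-up, "Mixed linear regression models adjusted for baseline will be used for the analyses of repeated outcomes". Under Methodological outcomes, the physical-activity contrast is to be analysed by ANCOVA or a mixed model, again adjusted for baseline.

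The Sample size calculation is "based on the intention-to-treat analyses of the primary effectiveness outcome QoL" and uses the same baseline-adjusted model. It shrinks the number of patients by the squared correlation between baseline and follow-up scores. That shows what baseline means here: the baseline value of the outcome, not a set of baseline characteristics that might include the stratum.

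The instrumental variable (IV) analysis, described under Effectiveness outcomes and in the Discussion, has no stated outcome-model covariates.

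**The concern.** Stratified allocation forces the arms to be alike in their mix of 12- and 18-month patients, which removes between-stratum variation from the true sampling variance of the treatment contrast. A model without the stratum leaves that variation in its residual. If the strata differ in outcome after baseline adjustment, the estimated standard error then exceeds the true one: confidence intervals are a little wide and the test rejects a little less often than it should.

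At stake is a modest amount of precision on the primary effectiveness outcome, and agreement between how patients are randomised and how they are analysed. The factor is known for every randomised patient, so using it needs no new data.

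**Working it through.** **Inputs from the Sample size calculation.** The planning difference comes from "we estimate a mean improvement of 13 points in the intervention group" against 6 points in controls: 13 − 6 = 7. The remaining inputs are "standard deviations of 17.7 and 17.1, power of 80% and alpha of 0.05, we calculated that 98 patients are needed in each group" and "we identified correlation of 0.4 between baseline and follow-up QoL".

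**Reproducing the plan's figures.**
- Pooled SD = √((17.7² + 17.1²)/2) = 17.40.
- n per group = 2 × (17.40 × (1.960 + 0.842)/7)² = 97.02, rounded up to 98. This agrees with the plan. Alpha must be two-sided, since one-sided gives 77.
- After baseline adjustment: 98 × (1 − 0.4²) + 1 = 83.3, stated as 83.

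Both figures reproduce, and neither takes any credit for stratification.

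**Effect of a stratum term.**
- Residual SD after baseline adjustment = 17.40 × √0.84 = 15.95, so the residual variance is 254.4.
- Let d be the difference in baseline-adjusted follow-up QoL between 12- and 18-month patients, and p the share of patients in one stratum. The stratum explains R² = p(1 − p)d²/254.4 of the residual variance.
- Omitting it inflates the estimated standard error by 1/√(1 − R²).

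The article gives neither d nor p, so both are assumptions. For p = 0.5:
- d = 2: R² = 1/254.4 = 0.4%
- d = 5: R² = 6.25/254.4 = 2.5%
- d = 10: R² = 25/254.4 = 9.8%

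**Simulation.** 20,000 runs per scenario, 83 per group, about equal strata, exact balance within strata, and total residual SD held at 15.95. Each cell shows the result without the stratum term, then with it.

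| Assumed gap d (points) | Mean SE | Power at 7 points | Type I error |
|---|---|---|---|
| 0 | 2.48 / 2.48 | 79.8% / 79.9% | 5.1% / 5.1% |
| 2 | 2.48 / 2.47 | 80.3% / 80.4% | 4.9% / 5.0% |
| 5 | 2.48 / 2.45 | 80.4% / 81.1% | 4.9% / 5.3% |
| 10 | 2.48 / 2.36 | 81.3% / 84.1% | 3.8% / 4.8% |

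The normal approximation for the model with the term gives 80.7%, 80.9%, 81.7% and 84.6% in the same order. With p = 0.3 it gives 80.7%, 80.8%, 81.5% and 83.9%, so an unequal split makes the gain smaller.

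**How large a gap would matter.** An R² of 2% gives a standard error ratio of 1/√0.98 = 1.010, and 5% gives 1/√0.95 = 1.026. With equal strata these need gaps of 2 × √(0.02 × 254.4) = 4.5 points and 2 × √(0.05 × 254.4) = 7.1 points. The upper one is about as large as the whole planned intention-to-treat effect of 7 points.

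**The case against.** The best counter-argument is that the text says adjusted for baseline, not adjusted for baseline only. A journal article condenses its protocol, and the covariate list may sit in an analysis plan that is not shown. This stands in part: a reader might infer that the investigators have decided to leave the stratum out, and no sentence says so. But the article is not silent on the model. It gives the adjustment in the same form for the 6-month, 6–24 month and physical-activity analyses, and sizes the trial on a baseline-adjusted model. The point is that the stated model does not reflect the stated design. For the IV analysis, where no covariates are given, the objection stands fully; including the stratum there is a matter of consistency only.

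The second objection is that little is lost, and this stands. Stratification balances the arms whichever model is fitted, and it still lowers the true variance of the contrast. What goes missing is the matching reduction in the estimated standard error. Much of any difference in QoL level between strata may also be absorbed by the baseline score.

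A reader might also take the 6-point improvement assumed in controls as evidence that 12- and 18-month patients differ. It is not. It is a mean change over a 12-week intervention period in a previous trial, and the same improvement in both strata would imply a stratum effect of zero.

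**Conclusion.** The point holds as a minor one. The models as written name baseline but not the factor used to stratify randomisation. If the strata differ in baseline-adjusted QoL, the result is a slightly overstated standard error and a slightly conservative test. At 83 per group the power cost is about 0 to 1 point for gaps up to 5 QoL points and about 3 points for a 10-point gap, which is the plan's full clinically relevant difference. This range rests on assumed gaps, equal strata, and a residual SD of 15.95 derived from the plan's own SDs and correlation.

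Three stronger readings are not supported:
- The benefit of stratifying is not thrown away, because balance and the lower true variance remain.
- The analysis is not biased and does not inflate type I error. Simulated type I error without the term lay between 3.8% and 5.1%.
- The sample size is not wrong on this account. The 98 and 83 per group reproduce without a stratum term, so its absence does not erode the planned 80% power.

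**What to change.** Add time since enrolment (12 or 18 months) as a fixed covariate, alongside the baseline score, in the 6-month linear regression, the 6–24 month mixed model and the physical-activity ANCOVA or mixed model. Carry the same covariate into the IV analysis so that its estimate is comparable with the intention-to-treat estimate. If an analysis plan not shown already does this, a sentence saying so is enough.

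The cost is one degree of freedom per model. No data collection and no change to the sample size are needed. Fixing the covariate before outcomes are compared also avoids a later choice about whether to include it.
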